	**Quality of care**
1. Secondary data analysis of: a) Obligatory and publicly reported quality indicators, b) Results of external quality audits	a) Self-assessed 15 indicators regarding the three themes: 1. Maintaining and promoting independence (e.g., in mobility), 2. Protection against health hazards and stress (e.g., in the development of pressure ulcers, falls, unintended weight reduction), 3. Support for specific needs (e.g., timeliness of the pain assessment, interaction with cognitively impaired residents) are assessed (percentage of residents with b) External quality audits assess 15 items regarding the four themes: 1. Support with mobility and self-care (e.g., support with eating and drinking, mobility, continence loss, continence promotion, personal hygiene, taking medication), 2. Support in coping with the demands and stresses of illness and therapy (e.g., taking medication, pain management, wound care), 3. Support in organizing everyday life and social contacts (e.g., impaired sensory perception, structuring the day, occupation and communication, nocturnal care), 4. Support in special needs and care situations (e.g., Support during the settling-in phase after moving in, transition management during hospitalization, support for residents with challenging behavior, use of measures involving deprivation of liberty)
2. Standardized survey of nursing home residents: a) ASCOT questionnaire b) EQ-5D and c) Proxy rating	a) Subjective care-related quality of life of nursing home residents is assessed in 8 dimensions: 1. Self-determination, 2. Personal hygiene and clothing, 3. Food and drink, 4. Feeling safe, 5. Talking and being together, 6. Spending time doing things you enjoy doing, 7. Clean, cozy home, 8. Influence of caregivers on self-esteem b) 5 dimensions of the health-related quality of life: 1. Mobility, 2. Self-care abilities, 3. Everyday activities, 4. Pain/ physical complaints, 5. Anxiety/depression c) 40 items in 10 subscales: 1. Relationship to nursing home staff^c^, 2. Positive affect^c^, 3. Negative affect^c^, 4. Restless/ tense behavior, 5. Positive self-image^d^, 6. Social relationships^c^, 7. Social isolation, 8 Feeling at home^d^, 9. Having something to do^d^, 10. Items without subscale
3. Standardized evaluation of shadowing data	PeBeM-indicators: 1. Actual number of provided interventions, 2. Targeted number of provided interventions, 3. Actual duration of the provided interventions 4. Targeted duration of the provided interventions 5. Actual extent of qualification fitting 6. Targeted extent of qualification fitting
4. Partially standardized survey of the shadowers	Qualitative assessment of the perception of care provision. The assessments will be developed and contain questions regarding: 1. Perception of communication and collaboration, 2. Perception of the interaction between nursing home staff and residents, 3. Perception of quality of care 4. Perception of the work organization
	**Job satisfaction**
Standardized survey of employees: a) Employee Experience Questionnaire (EXQ), b) StressBarometers	a) Two subscales with overall nine items regarding: 1. General job satisfaction (i.e., development opportunities, colleagues, work, management, remuneration), 2. Organizational commitment (i.e., concern for the institution's future, praise for the institution, pride in belonging to the institution, goodness of the employer) b) Three subscales regarding: 1. Organization and time management (4 items), 2. Tasks and content (20 items), 3. Collegial communication and exchange within the work (10 items)
	**Changes in actual-target difference**^**b**^
Shadowing^a^	Number of provided interventions Duration of the provided interventions Extent of qualification fitting

^a^ conducted in one living area in each facility from the intervention group

^b^ See Table 3

^c^Some of the items in the subscale are only applicable in QUALIDEM I (and not in QUALIDEM II for severe cognitive decline) ^d^All of the items of the subscale are only applicable in QUALIDEM I (and not in QUALIDEM II for severe cognitive decline)

Four different approaches are applied to assess the quality of care. A secondary data analysis of obligatory quality indicators will be conducted as a first step. In Germany, since 2022, these indicators have been reported publicly in every nursing home. As shown in Table 2, two different instruments were used: firstly, there will be an analysis of the 15 publicly reported self-assessed quality indicators. Secondly, the publicly reported results from the qualification audits from assessors and evaluators on behalf of the LTC insurance funds (i.e., Medizinische Dienste/medicproof GmbH) will be analyzed. These external quality audits collect data on 15 items in 4 themes (Table 2).

Secondly, paper-based surveys of nursing home residents will be carried out based on the ASCOT questionnaire (Adult Social Care Outcomes Toolkit) on their subjective quality of life [21, 22] and the EQ-5D about health-related quality of life in an evaluated German version [23]. The ASCOT is a care-related quality-of-life instrument with a high construct validity in the given setting [24]. To be able to record changes perceived by nursing home residents due to project-specific interventions (e.g., personnel and organizational changes in the care facility) that are not recorded in the ASCOT and the EQ-5D questionnaires, questions specially formulated for the project are added to the questionnaire (e.g., on satisfaction with organization and communication, perception of turnover of nursing home staff, etc.). In the t_1_ survey, further questions are included to identify the effect of the change, e.g., ‘Has anything changed as a result of the restructuring in the last year?’. For cognitively impaired nursing home residents, a proxy rating is provided via the QUALIDEM questionnaire [25, 26]. In German, the QUALIDEM is available in two versions according to the severity of cognitive decline (measured by the nursing home staff using the Global Deterioration Scale [27]). While QUALIDEM I can be applied in nursing home residents with mild cognitive decline (GDS Stadium 2–6), QUALIDEM II is used in residents with severe cognitive decline (GDS Stadium 7). The subscales of the QUALIDEM are shown in Table 2. The written survey and the proxy rating are planned for all nursing home residents living for at least four weeks in one of the participating nursing homes in both the intervention and the control group. The eligibility criteria are stated above. The surveys will be carried out in all living areas of the respective nursing homes.

Thirdly, empirical data will be collected in one living area of each nursing home of the intervention group in an observational study (‘shadowing’). The methodology was developed in the first PeBeM study and described in the final report [15]. The three elements of the data collection method are described in the background section. To assess actual-target differences (and their changes from t_0_ to t_1_), the shadowing data will be analyzed about (i) the number of interventions provided, (ii) the duration of the interventions provided, and (iii) the extent of qualification fitting. The determination of the respecting values is shown in Table 3.

**Table 3 Tab3:** Determination of actual and target data of care provision in the shadowing

Information provided in the data	Determination of the actual value	Determination of the target value	Involved Determiner
**Number** of provided interventions	Electronic time stamp while shadowing	1. DIP	1. Members of the study team qualified as a nurse
		2. Shadowers assessment	2. Shadowers
**Duration** of the provided interventions	Electronic time stamps while shadowing	Shadowers assessment	Shadowers
Extent of **qualification fitting**	Automatic electronic documentation while shadowing (data link in software between nursing staff and QL)	1. Software derives automatically from BI	1. Assessors and evaluators on behalf of the LTC insurance funds
		2. Software derives automatically from DIP (if additional information was registered)	2. As nurse-qualified members of the study team determine QL requirements individually

Fourthly, a partly standardized online questionnaire will be developed to assess the shadower's perception of the cooperation and communication structures within the nursing homes. The survey will be created based on experience from the PeBeM1 project.

Online surveys of the nursing staff will be conducted to assess job satisfaction. The standardized instruments used are the EXQ (Employee Experience Questionnaire) and the StressBarometer [28, 29]. The EXQ consists of four dimensions that address different aspects of job satisfaction. The two dimensions chosen for the study are i) overall job satisfaction and ii) organizational commitment. The other two dimensions addressing individual and collective engagement were excluded to minimize the time spent filling in the questionnaire and to increase the chances for participation in the survey. The EXQ was chosen because it is a standardized and evaluated instrument of good psychometrical quality (Cronbach’s alpha = 0.79—0.91, McDonald’s omega = 0.77 – 0.91), and it is easy to understand even if one is not a native speaker [28]. Furthermore, one of the dimensions directly addresses organizational commitment. As the intervention group in this study changes the work organization, these parameters are highly interesting for evaluating the intervention.

The StressBarometer was developed by the Federal Institute for Occupational Safety and Health (Bundesanstalt für Arbeitsschutz und Arbeitsmedizin – BauA) to record and assess psychological workloads within a job and was evaluated for many branches [29]. This instrument was chosen because it is easily understandable for non-native speakers. The utilization of the instrument in this study and the customization of the questionnaire (three subscales were selected) was permitted by the holder of rights (trade union ‘IG Metall’). The satisfaction in correlation to the restructuring of the work organization will be evaluated retrospectively at the facilities of the intervention group. The questions will be formulated during the project, taking into account the measures implemented for personnel and organizational development along with the implementation and service outcomes of the Proctor framework [30].

The focus groups, of which four are planned, are conducted after the other evaluation results have been analyzed. The focus groups aim to investigate (i) beneficial and inhibiting factors for the implementation process, (ii) positive and negative experiences during the process, and (iii) whether any practicable problem-solving scenarios can be taken into account when refining the algorithm. The guidelines for the focus groups will be based on the evaluation results and can, therefore, only be developed after the t_1_ survey.

## Prototypical concepts, strategy for a national rollout, and Algorithm 2.0

The study has three superordinated aims. The first is the participatory development of prototypical concepts for qualification-oriented work organization. According to individual nursing home characteristics like the care organization model, competency profiles of the staff, or the extent of digitalization, typed concept variants will be derived. The prototypical concepts thus consider different starting points of nursing homes and offer different development paths for various nursing homes. The definitive attributes that distinguish nursing homes with comparable preconditions will be analyzed using the iterative formal evaluation. These concepts, after rollout, can serve as templates for any nursing home from those to choose the most appropriate. Once one of the typed concepts is selected, any nursing home is free for individual adaptation. Due to the small sample size, the methodology for the analysis must be qualitative. However, the structure of the formative evaluation will take shape during the project. The final nursing home-typed concepts include procedures for a standardized census of the actual status as well as instruments and materials that depend on the prototype of the nursing home. The second final objective of the study aims to incorporate all the results and findings from project steps 1–4 and the contemporaneous participatory co-creative processes to parameterize *Algorithm 2.0*. Data from the shadowing (particularly the number of staff and data on the targeted duration of specific tasks and procedures) are analyzed to refine the algorithm. New aspects compared to *Algorithm* 1.0 will be (i) the incorporation of QLs 5 + and other professions in the calculation and (ii) target time values for indirect care and occasional care interventions. The third final objective is to develop a strategy for the national rollout. Methodological and substantive aspects for developing the nationwide rollout must be created during the project. The method under consideration is focus groups.

## Statistical analysis

No data will be collected during the development of an initial implementation concept, and no statistical analysis will be conducted. In the second work package, the actual status of the nursing homes, e.g., the infrastructure, the resident structure, the organization of the nursing homes, technical equipment, and the competencies of the staff, will be depicted. Information regarding the actual status will be analyzed descriptively.

The summative evaluation first analyzes the results of the mandatory external quality assessments descriptively. The analysis examines the development of the quality of care over the intervention period (t_0_, t_1_) in a pre-post comparison, both for the pertinent nursing homes and the control group, and the differences in the trends between them (difference-in-difference approach). Secondly, a descriptive analysis of the surveys on nursing home residents will be carried out. The analysis of the job satisfaction survey is carried out for the two subscales of the EXQ according to the method specified in the instrument. The subscales of the StressBarometer are not analyzed according to the specified scoring for workload but only in a descriptive comparison of the aggregated subscales and the individual items between the intervention and the control group and, in particular, for the indirect measurement of change in the intervention group (pre-post comparison). The analysis will examine changes in job satisfaction in t_1_ compared to t_0_ and if these changes differ between the intervention and control groups. Stratified evaluations are planned according to occupational groups and QLs. The answers to the questions on direct change measurement (t_1_ survey) will be analyzed quantitatively as far as possible; qualitative data will be summarized narratively if necessary. From the shadowing data of the intervention group, rates of the number and duration of the (non-)performance of the planned and the performed interventions are calculated (actual and targeted quantitative aspects of care). Furthermore, the change between t_0_ and t_1_ will be shown. Moreover, the analysis will examine the extent of qualification-oriented work organization and the change between t_0_ and t_1_ (actual and targeted qualitative aspects of care). The survey of the shadowers will be evaluated descriptively concerning the quality of care, possible causes of any deficits observed, and perceived changes due to the intervention.

The formative evaluation will be analyzed qualitatively due to the small sample size.

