Ten matched nursing homes as a control group do not undergo the two intervention measures but participate in the evaluation. Matching criteria are the federal state, number of beds, and ownership. The evaluation assesses (a) the quality of care, (b) the job satisfaction, and (c) the effects on the actual-target differences in number, duration, and QL fit of care provision as defined in step 3 (summative evaluation). QL-fit means that the required QL of the intervention (determined by the complexity of the intervention in interaction with the level of stability of the care situation of the nursing home resident) fits the QL of the nurse. Effects of the intervention concerning (a) and (b) will be measured using a difference-in-difference approach in the intervention and control group nursing home facilities. The difference in difference analysis can be applied when evaluating outcomes associated with healthcare policy implementation. This analysis's beneficial characteristic is the possibility of controlling for background changes [19]. The evaluation compares the pre- and post-intervention differences in outcomes in (a) and (b)—as operationalized below—between the treatment group (10 nursing homes retrieving the intervention) and the control group (10 nursing homes not retrieving the intervention). Endpoint (c) will only be investigated through a pre-post comparison with the intervention group, as the shadowing of the control group was regarded as too resource-intensive.

The study will involve 20 nursing homes in Germany (10 in the intervention group and 10 in the control group), nursing home staff, residents, about 120–150 data collectors (so-called ‘nurse shadowers’), and about 20 assessors and evaluators on behalf of the LTC insurance funds (Medizinische Dienste/medicproof GmbH). The respective work packages describe the participants' involvement in detail.

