## Summative evaluation

The customized concepts will be practiced, refined, and evaluated in the third study phase. The evaluation is planned as a prospective interventional study. In the intervention group, all elements of the data acquisition for the summative evaluation will take place as pre-post-comparison at two points in time (t_0_ before the intervention and t_1_ after the implementation of the changes in organization and staffing) at an interval of one year (note that the shadowing only takes place in one living area per care home). To control for general trends in the dynamic LTC setting and the effects of the revision of Paragraph 113 Section C of the German Social Code, Part 11 (that enacted a new finance of staffing ratios based on *Algorithm*
1.0) 10 nursing homes from the intervention group are matched with ten nursing homes in the control group by state, number of beds, and ownership. The control group undergoes the surveys of the summative evaluation but not the shadowing nor the two intervention measures. A (cluster) randomization was not possible due to the stipulations of the statutory order.

The summative evaluation assesses the effects of the intervention on (i) quality of care, (ii) job satisfaction, and (iii) changes in the difference between (a) the number of provided interventions, (b) the duration of the provided interventions, and (c) the extent of qualification-fitting. Table 2 provides an overview of the data collection methods for the endpoints of the summative evaluation.

**Table 2 Tab2:** Data collection methods for the endpoints of the summative evaluation

Methods and instruments	Operationalization of the endpoints

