## Limitations

As the duration of the intervention is short for the immense changes in the organizational structure and processes, the positive effect of the intervention may be underestimated. Furthermore, the restricted budget allowed us to select only ten facilities in the intervention group. This implies that we could only involve some German states. As the final selection resides by the funder, selection bias could occur. In those ten facilities, the shadowing will be performed only in one of the living areas, so the transferability of the results to the whole facility may be restricted. The transferability of the customized concepts is limited as the number of participating nursing homes is restricted to ten. However, the prototypical concepts developed for the national rollout are open for individual adaptation and thus can be applied in every German nursing home.

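### The plan promises to measure effects in 10 against 10 homes, but most controlled comparisons are only descriptive and no main outcome is named, so an effect cannot be told from ordinary variation between homes

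*Protocol article*

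**What the plan says.** - **Hypothesis.** The Objectives section expects improvement in two whole domains, job satisfaction and quality of care, and refers to the methods for their definition.
- **Contrast.** Study design and participants: "Effects of the intervention concerning (a) and (b) will be measured using a difference-in-difference approach in the intervention and control group nursing home facilities". There, (a) is quality of care and (b) is job satisfaction.
- **Homes.** Summative evaluation: "10 nursing homes from the intervention group are matched with ten nursing homes in the control group by state, number of beds, and ownership". Randomisation was not possible, and Recruitment says the funder made the final choice of intervention homes. On the number of homes, Limitations says "the restricted budget allowed us to select only ten facilities in the intervention group".
- **Measures.** Table 2 lists many, for example "Self-assessed 15 indicators regarding the three themes" and "External quality audits assess 15 items regarding the four themes". None is marked as primary.
- **Analysis.** Statistical analysis: "The summative evaluation first analyzes the results of the mandatory external quality assessments descriptively". The next sentence adds the difference in trends between the two groups. Resident surveys are also analysed descriptively, and StressBarometer subscales and items are compared descriptively. The two EXQ subscales follow the instrument's own method. For job satisfaction the question is whether there are changes and "if these changes differ between the intervention and control groups". Stratified evaluations by occupational group and qualification level are also planned.

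**The concern.** The stated aim and the stated analysis do not match. A directional hypothesis and the promise to measure effects call for an estimate with its uncertainty. The intervention is applied to whole homes, so the relevant uncertainty is how much homes differ in their change from t0 to t1. A descriptive contrast of two groups of ten homes does not show this. A reader could not judge whether a difference exceeds ordinary variation, or whether a small difference means no effect or too little information.

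The unnamed main outcome adds to this. With two broad domains and many measures, any favourable measure could later be presented as the improvement that was predicted. The Objectives section says the rollout strategy will be derived from the evaluation findings. Limitations covers short duration, funder selection and transferability, but not imprecision or the number of outcomes.

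**Working it through.** The article states no sample size calculation, power, significance level or effect size, so there is no figure to reproduce. The 5% level and 80% power below are assumptions.

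**1. Measures available in both groups (Table 2)**

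| Source | Count |
|---|---|
| Self-assessed quality indicators | 15 |
| External audit items | 15 |
| ASCOT dimensions | 8 |
| EQ-5D dimensions | 5 |
| QUALIDEM subscales (tenth entry, items without a subscale, left out) | 9 |
| EXQ subscales | 2 |
| StressBarometer subscales | 3 |
| **Total** | **57** |

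The StressBarometer items, which the plan also compares singly, add 4 + 20 + 10 = 34, giving 57 + 34 = 91 before stratification. At the other extreme there are 7 sources. The count describes instrument content: except for the StressBarometer items, the article does not say that each entry is analysed separately. Shadowing outcomes are left out because the control group is not shadowed.

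**2. Precision with 10 + 10 homes**

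Let SD_h be the standard deviation, between homes in one group, of the t0-to-t1 change. Let SD_p be the standard deviation of the pair-level difference-in-difference.

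| | Unpaired, 18 df | Ten pairs, 9 df |
|---|---|---|
| Standard error | √(2/10) = 0.447 SD_h | 1/√10 = 0.316 SD_p |
| 95% half-width | 2.101 × 0.447 = 0.94 SD_h | 2.262 × 0.316 = 0.72 SD_p |
| Detectable (non-central t) | 1.32 SD_h | 1.00 SD_p |

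**3. Does pairing help?**

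The columns use different units: SD_p = SD_h × √(2(1 − r)), where r is the within-pair correlation of changes. At r = 0 the paired analysis detects 0.996 × √2 = 1.41 SD_h, which is worse than 1.32. Pairing gains when 0.996 × √(2(1 − r)) < 1.325, that is, when r exceeds about 0.12. The documents give no value for r.

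**4. What a bare difference can look like under no effect**

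With ten pairs and normal approximation, a mean beyond ±0.3 SD_p has probability 2 × [1 − Φ(0.3 × √10)] = 0.34. Beyond ±0.5 SD_p it is 0.11. If all 57 entries were compared, about 57 × 0.343 = 19.5 and 57 × 0.114 = 6.5 would pass these marks by chance, in either direction. The marks are illustrative; the plan sets no threshold.

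**The case against.** The strongest defence is that this is a condensed article. Standard errors, intervals, clustering and use of the matching are commonly left to a full protocol or analysis plan, and neither is shown. That stands for silence alone, so the missing home-level error measure is the weaker half of the point. However, the section on statistical analysis positively calls several comparisons descriptive, while the design section promises effects. Naming the main outcome belongs in a protocol and does not depend on the unseen plan.

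A second defence is that description suits ten homes. That is reasonable, but then the hypothesis and the language of effects should be softened. An interval and a plot of home values also serve description.

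Several stronger readings are tempting but not supported:

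- *Staff and residents are pooled as independent, which inflates false positives.* Under assumed home sizes and correlations, a respondent-level 5% test could err in 7% to 32% of cases. No such test is stated, and the design section contrasts homes with homes. Thirty of the listed measures (15 + 15) are reported quality indicators and audit items with no staff respondents to pool.
- *Everything is descriptive.* This is not said of the two EXQ subscales.
- *Dozens of outcomes will each be tested, and chance findings declared effects.* No test or decision rule is stated.
- *The ten pairs are wasted.* One-to-one pairing is an inference from ten homes being matched with ten, and pairing could even cost precision.
- *The rollout rests on these contrasts alone.* Focus groups are the method under consideration for it.

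**Conclusion.** The point holds in a limited form. The article states a directional hypothesis and a difference-in-difference evaluation of effects. It then makes the comparisons of quality assessments, resident surveys and StressBarometer descriptive, leaves the EXQ comparison without any stated measure of uncertainty, and names no main outcome. An analysis that follows this text could not separate an effect from ordinary differences between homes, and it leaves open which measure decides whether the hypothesis is supported.

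The size is that of a small home-level comparison: about 1.3 SD of home-level change is detectable unpaired, or about 1.0 SD of the pair-level difference, under the assumed 80% power and two-sided 5%. The figure of about 57 measures is an upper count of instrument content without single StressBarometer items and strata; it is not a number of planned tests. The article does not show that chance differences will be misread, only that nothing in the stated plan guards against it. This should be corrected, and no new data are needed.

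**What to change.** - Before t1 results are seen, name one headline outcome per domain, for example EXQ general job satisfaction and the ASCOT score. Label all other measures and strata as supportive.
- For each headline outcome, and preferably the other controlled outcomes, compute every home's t0-to-t1 change. Report the intervention-minus-control difference with a 95% interval based on variation between homes: t with 18 df, or the ten pairs with 9 df if matching is one-to-one. Fix that choice in advance.
- Add a plot of the home or pair values.
- Do not add p-values for every outcome. They would increase the multiplicity, and permutation p-values would have no randomisation basis here.
- State that intervals do not address the non-random, funder-made selection of the intervention homes.
- If a full analysis plan already contains these elements, refer to it and align the wording of the Statistical analysis section.

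The cost is wording and simple computation. The drawback is that intervals will be wide and some apparent effects will not stand.
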